### Laboratory tests

*Antibodies to human influenza viruses*

The level of antibodies to influenza antigen in the plasma taken on days 0, 28 and 56 will be determined using an enzyme-linked immunosorbent assay (ELISA). Briefly, 100 μL of the flu vaccine (1 μg/mL) in coating buffer (Thermo Fischer Scientific, USA) will be added to 96-well ELISA plates (Corning C62-9018 plate) and incubated at 4°C for 24 hours. The plate will be washed thrice with 250 μL of ELISA wash buffer (Thermo Fischer Scientific, USA). Then, the plate will be blocked with 250 μL of ELISA diluent (Thermo Fischer Scientifc, USA) at room temperature for 2 hours. The plate will be washed thrice with 250 μL of ELISA wash buffer (Thermo Fischer Scientific, USA). The plate will be dried by gently tapping on absorbent paper. Then, 100 μL of diluted human serum (baseline, Day 28 and Day 56) will be added to each well in duplicates. A standard curve of anti-influenza A (Santa Cruz, USA) and anti-influenza B (Santa Cruz, USA) antibodies will be used to quantify anti-influenza A and anti-influenza B levels in the serum of healthy volunteers at different time points. Blank wells will contain 100 μL of ELISA diluent (Thermo Fischer Scientific, USA). After 2 hours at room temperature, the plate will be washed five times with 250 μL of ELISA wash buffer (Thermo Fischer Scientific, USA). Then, 100 μL of anti-human Ig (IgG, IgM and IgA) or anti-human IgG conjugated with horseradish peroxidase (HRP) (Abcam, USA) will be added to all wells. After one hour at room temperature, the plate will be washed five times with 250 μL of ELISA wash buffer (Thermo Fischer Scientific, USA), and 100 μL of TMB ELISA substrate (Abcam, UK) will be added to all wells. The enzymic reaction will be stopped after 10-20 mins by adding 100 μL Stop solution for TMB substrate (Abcam, UK). Absorbance at 450 nm will be read using a microplate reader (Tecan, Switzerland).

*Antigen-specific proliferation*

The buffy coat will be isolated from peripheral blood and cultured in the presence of the influenza vaccine for 72 hours. The antigen-specific proliferation will be measured using a commercial cell proliferation kit. The culture supernatant will be harvested and stored at -80°C until used for cytokine analysis.

*Plasma levels of vitamin E*

Plasma levels of vitamin E will be quantified from samples taken on days 0, 28 and 56 using the high-performance liquid chromatography (HPLC) [Agilent HPLC 1200 with fluorescence detector, Agilent, USA] as desbribed previously.
^
36
^ Briefly, 1.0 mL of 0.9% sodium chloride (NaCl) will be added to 1.0 mL of human plasma in a glass test tube and vortexed for 30 seconds. Then, 1.0 mL ethanol-BHT (0.625 mg/mL) will be added, and the mixture will be vortexed for 30 seconds. Following this, 5.0 mL of n-hexane-BHT (0.05 mg/mL) will be added, and the mixture will be shaken overnight for 16 hours at 250 rpm, at 10°C using a shaking incubator (WIS-20, Witeg, Germany). After centrifugation (2500 rpm for 15 minutes at 4°C), the upper organic layer will be carefully extracted and transferred to a sterile tube. The tubes will be evaporated to dryness using a speed vacuum concentrator with CoolSafe -110°C cold trap (MaxiVac, LaboGene, Denmark). To obtain a standard curve for quantification, standard tocopherols (Toc) and tocotrienols (T3) (Hovid, Malaysia) will be separated on a Phenomenex KinetexTM PFP column (5.0 μm, 150 × 4.6 mm; Phenomenex) with a guard column using MeOH/H
_2_O (87:13) as an eluent at a flow rate of 0.9 mL/min. The dried samples will be reconstituted with 0.3 mL of mobile phase [methanol (MeOH) + butylated hydroxytoluene (BHT) (0.625 mg/mL)] and filtered using a nylon syringe fitted with a 0.45 μm, 4 mm filter (Chrominex, Singapore) prior to HPLC analysis. Then, 10 μL of the preparation will be injected into the HPLC (Agilent HPLC 1200, USA). The fluorescence detector will be set an excitation wavelength of 296 nm and emission wavelength of 325 nm and photomultiplier tube (PMT) gain will be set at 10.

*Cytokines*

Plasma and culture supernatant stored at -80°C will be thawed and used to quantify plasma levels of cytokines [e.g. interferon-gamma (IFN-γ) (MABtech, USA), tumour necrosis factor-alpha (TNFα) (MABtech, USA), interleukin-12 (IL-12) (MABtech, USA), and interleukin-17A (IL-17A) (MABtech, USA)] using commercial ELISA kits.

*Protein expression*

The plasma protein concentrations will be determined using a commercial Bradford test. The plasma will be subjected to albumin and immunoglobulin elimination steps using the Pierce albumin/IgG removal kit (ThermoScientific, USA). Then, the protein will be processed using the EasyPep™ Mini MS Sample Prep Kit (ThermoScientific, USA) before being analysed with liquid chromatography-mass spectrometry/mass spectrometry (LCMS/MS) (Agilent, USA) to identify differentially expressed proteins (DEP). The expression of the selected DEP will be verified using ELISA or Western blotting.

*Gene expression studies*

Total RNA will be extracted from 1.5 mL of freshly drawn blood using a commercial ribonucleic acid (RNA) extraction kit (QIAGEN
^®^ RNA Blood Mini kit, QIAGEN GmBH, Hilden, Germany). Briefly, the red blood cells (RBC) will be lysed by adding 7.5 mL RBC lysis buffer (provided with RNA extraction kit, (QIAGEN, Germany). The mixture will be incubated on ice for 15 min, and the buffy coat will be recovered by centrifugation (10 min at 4°C). The supernatant will be discarded, and the pellet will be washed twice with 3 mL of the RBC lysis buffer and recovered by centrifugation (10 min at 4°C). Then, RNA will be extracted using RNA extraction, as recommended by the manufacturer (QIAGEN, Germany). The extracted RNA’s purity, quality, and integrity will be assessed using NanoDrop
^®^ ND-1000 (NanoDrop Technologies Wilmington, DE, USA) and Agilent 2100 Bioanalyzer (Agilent Technologies Santa Clara, CA, USA). The primers related to various genes associated with T-helper (Th) and T-regulatory (Treg) cells (
*Hoxa10, GATA3, RORα, CCR5, CXCR3 CCR7, IL-24, IL-12β2R, FoxP3; CD49b, folate receptor-4*) will be synthesised commercially (IDT Integrated DNA Technologies, Singapore). Quantitative PCR (QPCR) will be performed to compare mRNA expression between the groups and within the group (day 0 and day 56). The purified RNA will be processed using qPCRBIO SyGreen 1-Step Detect LOW-ROX kit (CAT#PB25.11-01), (QIAGEN, Hilden, Germany) for complementary DNA (cDNA) synthesis according to the manufacturer’s instruction. The total reaction volume per sample will be 20 μL with 10 ng of RNA template, 2 ng/μl of forward and reverse primers. Each sample will be analysed using commercial primer sets various genes associated with T-helper (Th) and T-regulatory (Treg) cells (Hoxa10, GATA3, RORα, CCR5, CXCR3 CCR7, IL-24, IL-12β2R, FoxP3; CD49b, folate receptor-4), which will be synthesized commercially (IDT Integrated DNA Technologies, Singapore). The GAPDH gene will be used as the housekeeping gene to normalize the quantitative polymerase chain reaction (QPCR) data. The cycling protocol will consist of 40 cycles involving denaturation at 95° for 5 seconds, followed by annealing and extension- steps, each at 60°C for 30 seconds. All samples will be run in triplicates. At the end of the 40 cycles, a dissociation curve analysis will be performed to confirm amplification specificity using the optical module PCR detection system available in the thermocycler (QuantStudio™ 5 Real-Time PCR System, Applied Biosystem, Thermo Scientific, USA). The ratio of gene expression of the target gene was compared between undifferentiated and differentiated cells using the formulae: 2-(ΔCt (test gene) – ΔCt (GAPDH)), where ΔCt represents the difference of threshold cycle (Ct) for each target gene.

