### Intervention

The TRF used in this study will be Tocovid Suprabio
^TM^, manufactured by HOVID Ltd in Malaysia, and is a registered supplement in Malaysia that is sold as an over the counter (OTC) supplement in major pharmacies in Malaysia. The active ingredient of the Tocovid SupraBio
^TM^, called EVNol
^TM^ was manufactured by ExcelVite Sdn. Bhd., Malaysia. The TRF has received the generally regarded as safe (GRAS) status by the USA Food Development Authority (FDA).
^
35
^

The influenza vaccine used in this study will be the VaxigripTetra Influenza vaccine type A and B as per the WHO recommendations, which will be obtained from the Thomson Hospital’s pharmacy.

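### The ELISA as written cannot give separate anti-influenza A and anti-influenza B levels: one mixed coat and one absorbance yield a single total signal

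*Protocol article*

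**What the plan says.** The antibody assay is set out in the Laboratory tests section of the protocol article, under antibodies to human influenza viruses. Its steps are:

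- **Coat:** "100 μL of the flu vaccine (1 μg/mL) in coating buffer". No other coating antigen is described.
- **Sample:** "100 μL of diluted human serum (baseline, Day 28 and Day 56) will be added to each well in duplicates".
- **Calibration:** "A standard curve of anti-influenza A (Santa Cruz, USA) and anti-influenza B (Santa Cruz, USA) antibodies", which "will be used to quantify anti-influenza A and anti-influenza B levels in the serum of healthy volunteers at different time points".
- **Detection:** "100 μL of anti-human Ig (IgG, IgM and IgA) or anti-human IgG conjugated with horseradish peroxidase (HRP"), followed by substrate and a single absorbance reading at 450 nm.

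The coating vaccine is not named in that section. The only influenza vaccine named anywhere in the article is in the Intervention section: "the VaxigripTetra Influenza vaccine type A and B as per the WHO recommendations".

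The Abstract, Objectives and Outcomes sections refer to antibody against influenza in general and do not divide it into A and B.

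**The concern.** In an assay of this form, the coating antigen decides which antibodies are captured, and the conjugate decides which class of captured antibody is seen. Here the coat carries both A and B antigens, and neither conjugate option separates antibody to A from antibody to B. The only element that differs between A and B is the pair of standards. A standard curve converts an absorbance into a number; it cannot add a specificity that the coat and the conjugate lack.

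Anyone following these steps would therefore report an A level and a B level that are not what their labels say. A rise in antibody to one type alone would appear under both labels. The concentrations would also lack a defined scale, because the same serum can receive two different values depending on which curve is used. Antibody to influenza is the first-listed primary outcome, so the labelling of its read-out matters.

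**Working it through.** The plan gives no figure to reproduce here. The check asks whether A and B can be recovered from what is measured.

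**Inputs from the Laboratory tests section:** one coat, the vaccine; one absorbance per well; two standards, anti-A and anti-B. **Input from the Intervention section:** the vaccine contains A and B antigens. **Assumed for illustration:** signal is linear in antibody content, and the numerical contents and signal factors are invented.

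**Step 1. The signal.** Let a serum contain A units of anti-A and B units of anti-B antibody, with signal per unit kA and kB. One well gives

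S = kA·A + kB·B.

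This is one equation in two unknowns: the measurement matrix [kA kB] has rank 1. Adding wells does not help, because every well has the same coat and gives the same equation apart from assay noise.

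**Step 2. The two readings.** The anti-A curve returns S/kA and the anti-B curve returns S/kB. Their ratio is kA/kB, whatever the serum contains, so the second reading adds nothing to the first.

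**Step 3. Numbers, with kA = 1.** S = A + kB·B; A-curve reading = S; B-curve reading = S/kB.

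| kB/kA | True (A, B) | S | A-curve reading | B-curve reading |
|---|---|---|---|---|
| 1 | (10, 90) | 10 + 90 = 100 | 100 | 100 |
| 1 | (50, 50) | 50 + 50 = 100 | 100 | 100 |
| 1 | (90, 10) | 90 + 10 = 100 | 100 | 100 |
| 0.5 | (10, 90) | 10 + 45 = 55 | 55 | 110 |
| 0.5 | (50, 50) | 50 + 25 = 75 | 75 | 150 |
| 0.5 | (90, 10) | 90 + 5 = 95 | 95 | 190 |
| 2 | (10, 90) | 10 + 180 = 190 | 190 | 95 |
| 2 | (50, 50) | 50 + 100 = 150 | 150 | 75 |
| 2 | (90, 10) | 90 + 20 = 110 | 110 | 55 |

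No reading equals the true A or B content. At kB/kA = 2, the A-curve reading falls from 190 to 110 as true A rises from 10 to 90. The total is not on a fixed scale either: the serum (50, 50) holds 100 units, but at kB/kA = 0.5 it reads 75 on one curve and 150 on the other.

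**Step 4. Type-specific coats.** With separate A-only and B-only wells and no cross-binding, the matrix is diagonal with entries kA and kB. Its rank is 2 for 2 unknowns, so both levels can be recovered.

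**The case against.** The strongest reply is that no stated outcome needs the split. The Outcomes section and the first objective refer to influenza antibody as a whole, and the assay as written can still deliver a total anti-vaccine signal on which randomised arms can be compared. This stands, and it limits the point. A reader might infer that the primary outcome is unmeasurable; the documents do not support that.

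The method is also introduced as a brief account in a condensed article, and the coating product is identified only by inference from the Intervention section. The inference is reasonable, since no other influenza vaccine appears. Brevity does not rescue the text: a fuller procedure would have to replace the stated coating antigen, not merely add detail to it.

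Three stronger readings are tempting and should not be made:

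- **That A and B will be presented as two confirming endpoints.** No section defines two antibody endpoints or plans to test them separately.
- **That the standard curves will fail because the purchased standards are not human.** Their species is not stated, so this cannot be settled from the documents.
- **That results will be non-comparable because two conjugates are mixed.** The wording "anti-human Ig (IgG, IgM and IgA) or anti-human IgG conjugated with horseradish peroxidase (HRP") may describe two separate read-outs. It leaves open which one is primary, but does not say that they will be used interchangeably.

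**Conclusion.** The point holds in a limited form. As written, the assay yields one total anti-vaccine signal, and the claim to quantify anti-A and anti-B levels separately is wrong. This is a contradiction between the stated steps and the stated output, not a missing detail. It would affect the labelling and scale of every antibody result, at most 150 × 3 = 450 samples before dropout. That count shows the reach of the mislabelling; it does not measure bias or loss of power, and neither is shown here. The comparison of arms on total anti-vaccine antibody is unaffected.

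The conclusion assumes that the coat is the A and B vaccine named under Intervention and that no unreported step separates the two types. It does not depend on the invented values in the table, on linearity, or on which conjugate is used: the total-Ig option detects IgG, IgM and IgA and the other detects IgG only, but neither distinguishes A from B.

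**What to change.** In the Laboratory tests section, define the antibody outcome as a single anti-vaccine antibody level in relative units, read from one common reference. Name one conjugate for the primary read-out, either total Ig or IgG, and delete the statement that A and B levels will be quantified separately. This needs a change of wording and a common reference material. The cost is giving up type-specific statements, which the Abstract, Objectives and Outcomes sections do not promise.

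If separate A and B levels are wanted, coat separate wells with A-only and B-only antigen and read each on its own standard. That requires type-specific antigen and additional wells, and it relies on little cross-binding between the types.

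The Study status section says that volunteers are still being screened, so the change can be made before outcome results accumulate. The Study plan already uses a screening antibody level to select volunteers without naming its assay; if the same ELISA is meant, the same definition should apply there.

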## Objectives

This study aims to investigate the effects of different concentrations of TRF (400, 200, 100 or 50 mg) on the immune response to an influenza vaccine in healthy individuals and to elucidate the mechanism of action. Using high and low dosages is important to understand what may happen following TRF supplementation. This information can be used to develop this in a range of functionality. The specific objectives are (i) to compare antibody responses to influenza antigen following daily supplementation with TRF (400, 200, 100 or 50 mg) with placebo; (ii) to compare leucocyte profiles and cytokine levels in response to influenza antigen following daily supplementation with TRF (400, 200, 100 or 50 mg) with placebo; (iii) to identify differentially expressed plasma proteins following daily supplementation with TRF (400, 200, 100 or 50 mg) with placebo in the presence or absence of vaccination; and (iv) to correlate plasma vitamin E levels with antibody levels in volunteers with and without daily supplementation with TRF.

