### Outcomes

The primary outcomes of this trial will be comparing the antibody levels to influenza, the blood leucocyte profile, plasma vitamin E and cytokine production between the different groups. Secondary outcomes will be correlating plasma vitamin E levels with immune responses, plasma proteins and gene expression patterns.

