### Sample size

The sample size was calculated using
G*Power version 3.1.9.4. With the power set at 80% and a 5% level of significance, the analysis showed that 26 subjects per arm were required to detect a large difference between groups. The effect size (d) was assumed to be 0.7, based on a previous study.
^
19
^ Assuming a 15% dropout rate in two months, 30 subjects per arm (150 subjects) will be enrolled.

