### Statistical analysis

Statistical Package for the Social Sciences (
SPSS) version 18 will be used for the statistical analysis. The mean and standard deviation values will be calculated for each parameter and compared with the baseline and/or placebo. Differences between the baseline and/or placebo will be tested using a paired-t-test when data are normally distributed or Wilcoxon signed-rank when the data are skewed. The significance level will be set as a P value of ≤ 0.05.

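### The only decision rule, an unadjusted P ≤ 0.05 for every parameter, also covers the LC-MS/MS protein screen, where many false calls would be expected if TRF has no effect

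*Protocol article*

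**What the plan says.** Objective (iii) in the Protocol article is "to identify differentially expressed plasma proteins following daily supplementation with TRF (400, 200, 100 or 50 mg) with placebo", both with and without the vaccine. Under Laboratory tests, Protein expression, LC-MS/MS is used "to identify differentially expressed proteins (DEP). The expression of the selected DEP will be verified using ELISA or Western blotting". That section gives no threshold for calling a protein differentially expressed (a DEP), no number of proteins, no sampling days for the screen, and no statement of which samples go into the second assay.

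Statistical analysis is one paragraph. Its scope is general: "The mean and standard deviation values will be calculated for each parameter and compared with the baseline and/or placebo". Its test is also general: "Differences between the baseline and/or placebo will be tested using a paired-t-test when data are normally distributed or Wilcoxon signed-rank when the data are skewed". Its decision rule is "The significance level will be set as a P value of ≤ 0.05". No outcome is exempted and no multiplicity rule is given.

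Under Outcomes, plasma proteins are not primary: "Secondary outcomes will be correlating plasma vitamin E levels with immune responses, plasma proteins and gene expression patterns". The five arms in Table 1 are the only enrolled population described.

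**The concern.** A 5% error rate per test is meant for a few planned comparisons. A protein screen makes hundreds, so a fixed share of null proteins will be called in every contrast.

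The second assay looks like a safeguard, but its value depends on whose plasma is measured. If the arms differ by chance in a protein, that imbalance is in the plasma itself, and a second assay of the same plasma will tend to show it again.

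The rule also permits comparison with baseline alone. Within a TRF arm, Day 56 against Day 0 would pick up effects of the vaccine or of time even if TRF does nothing, and a second assay would confirm those as well.

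At stake is the protein part of the mechanism aim: proteins could be reported as TRF-responsive when they are chance findings.

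**Working it through.** **The plan's own figure.** None is given for the screen. The one computed figure is the sample size: "With the power set at 80% and a 5% level of significance, the analysis showed that 26 subjects per arm were required", with d = 0.7. A one-sided two-sample t-test reproduces it (25.9, rounded up to 26; power 80.1%). Two-sided, 26 per arm has 69.7% power. The sidedness does not affect this point; 26 per arm is used below only as the analysed number.

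**Inputs.** From the article: P ≤ 0.05, four doses against one placebo arm, 26 per arm. Assumed: m = 100 to 500 quantified proteins, and between-assay correlation ρ = 0.3 to 0.9. Simulations use unpaired t-tests, because volunteers in different arms are not paired. Any valid 5% test has the same error rate per protein.

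**Screen, no TRF effect.** Expected false calls over four contrasts = m × 0.05 × 4.
- m = 100: 5 per contrast, 20 in all
- m = 300: 15 per contrast, 60 in all
- m = 500: 25 per contrast, 100 in all

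Simulation agrees. Because the contrasts share a placebo arm, these calls fall on about 15, 47 and 78 distinct proteins.

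Chance of at least one false call in a single contrast, independent proteins = 1 − 0.95^m: 92% for m = 50 and 99.4% for m = 100. Over four contrasts, simulation gives about 99% or more for m = 100 to 500, with proteins independent or correlated at 0.5.

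**Second assay on the same plasma.** Two measurements with correlation ρ were simulated in the same null volunteers. The share of false calls that pass again at P ≤ 0.05 in the same direction is:

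| ρ | Pass again |
|---|---|
| 0 (new volunteers) | 2.5% |
| 0.3 | 9% |
| 0.5 | 18% |
| 0.7 | 32-33% |
| 0.9 | 58-59% |

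Among the strongest screening hits (P ≤ 0.005) the share is 30% at ρ = 0.5, 60% at 0.7 and 95% at 0.9.

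For m = 100 with every call re-assayed, the expected number of verified false calls over four contrasts is 20 × 0.09 = 1.8 at ρ = 0.3 and 20 × 0.18 = 3.6 at ρ = 0.5. Per contrast these are 0.4 and 0.9.

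**Chance of at least one verified false protein per null trial.** About 65-100% if every call is re-assayed, and about 31-100% if only the top three are, for ρ = 0.3 to 0.9.

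**With Benjamini-Hochberg at 5%, no TRF effect.** The chance of any false call is about 5% per contrast, and about 3-7% in simulation pooled over the four contrasts.

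**The case against.** The strongest reply is that the article never says in words that a DEP is a protein with P ≤ 0.05. It is a condensed text, and a false-discovery rule for a secondary omics outcome could sit in an analysis plan that is not shown. That stands as far as it goes: the threshold is inferred. But the article does more than stay silent. It states a rule for each parameter and exempts nothing, so a reader applying it reaches P ≤ 0.05 for proteins. If another rule exists, this text contradicts it.

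Three stronger readings are tempting, and the documents do not support them.
- **That verification is done in the same volunteers.** The article names no samples. It describes no other plasma, so this is the natural reading, but it remains conditional.
- **That the article offers verification as proof against chance.** It says only that expression will be verified, which fits a check of the measurement.
- **That a verified list is practically certain under no effect, or would look much the same whether or not TRF acts.** The near-certainty applies to the screen alone. After the second assay the chance can be as low as about 31%, depending on the number of proteins, the correlation and how many are selected, none of which is given. No scenario with a true TRF effect was examined.

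**Conclusion.** The point holds in conditional form. Read as written, the general rule governs the protein screen. With no TRF effect it would be expected to give about 20-100 false DEP calls, at least one of them almost surely. This rests on the assumed 100-500 proteins, though even 50 proteins give a 92% chance of a false call in a single contrast.

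If the ELISA or Western blot step uses the trial's own plasma, it cannot separate chance differences from real ones: 9-59% of false calls would pass again for assumed correlations of 0.3-0.9, against 2.5% in new volunteers. How many false proteins would end up verified cannot be fixed from the article.

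The outcome is secondary, so the trial's main comparisons are untouched. The change is still worth making, because the stated rule gives a misleading result when applied to the screen.

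**What to change.** In Laboratory tests (Protein expression) and Statistical analysis:

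1. Exempt the LC-MS/MS screen from the unadjusted P ≤ 0.05 rule.
2. Call a protein differentially expressed only if its between-arm TRF-versus-placebo comparison has a Benjamini-Hochberg adjusted P ≤ 0.05 across all quantified proteins and all doses, at each time point analysed. Use an unpaired test or a baseline-adjusted model, not a paired test across arms or a within-arm comparison with baseline.
3. Select proteins for ELISA or Western blot from that list, and label any others exploratory.
4. State which samples the second assay uses. If they are the trial's own, report the step as technical confirmation of the measurement only.

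The cost is a few sentences, with no new samples or assays. The downside is a shorter DEP list and less power for a single protein with a modest true effect; such proteins can still be listed as exploratory.

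### The gene-expression ratio is defined for cell states the trial does not have and names no calibrator for ΔCt; the contrast needs correcting, though the algebra can stay

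*Protocol article*

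**What the plan says.** All of this is in the Protocol article. Under Laboratory tests, Gene expression studies:

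- **Purpose.** Quantitative PCR is done "to compare mRNA expression between the groups and within the group (day 0 and day 56").
- **Material.** "Total RNA will be extracted from 1.5 mL of freshly drawn blood"; red cells are lysed and the buffy coat is recovered for extraction.
- **Reference gene.** "The GAPDH gene will be used as the housekeeping gene to normalize" the data.
- **Ratio.** The subsection closes by saying that the target-gene ratio was "compared between undifferentiated and differentiated cells". The formula is printed as "2-(ΔCt (test gene) – ΔCt (GAPDH" and closing brackets. I take the lost superscript as an effect of text conversion and read the formula as 2 to the power of minus the bracket.
- **Definition of ΔCt.** "where ΔCt represents the difference of threshold cycle (Ct) for each target gene".

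The Outcomes section gives the role of the measure: "Secondary outcomes will be correlating plasma vitamin E levels with immune responses, plasma proteins and gene expression patterns". The Statistical analysis section says each parameter is compared with baseline and/or placebo.

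**The concern.** The sentence that defines the quantity to be computed names a contrast between two cell states. Nothing else in the article mentions undifferentiated or differentiated cells. The sentence is in the past tense, in a protocol still at the screening stage, and reads like text carried over from a cell-culture experiment.

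The definition of ΔCt does not repair this, because it does not say which two threshold cycles are subtracted. They could be two genes in one sample or two conditions for one gene. These give different variables: a level relative to GAPDH, or a change over time. Eleven genes are listed, and both the arm comparisons and the correlations with plasma vitamin E depend on which variable is used. If the choice stays open until the data are in hand, it can be made after the results are seen.

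**Working it through.** The article gives no numerical result for this outcome, so there is no figure to reproduce. The check sets the statements side by side and works the formula through under each reading of ΔCt.

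**1. Does the named contrast exist in the trial?**

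- RNA source: fresh blood, with no culture and no differentiation step.
- The only cell culture described is under Antigen-specific proliferation, where buffy coat is "cultured in the presence of the influenza vaccine for 72 hours". It serves proliferation and cytokine measurement and is not the RNA source.
- Contrast stated in the same subsection: between groups, and Day 0 against Day 56.

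The contrast attached to the formula therefore has no counterpart in the trial and conflicts with the one stated in the same subsection.

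**2. What does the formula give?** Write it as R = 2^-(ΔCt(target) − ΔCt(GAPDH)).

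- *Reading A:* ΔCt is the Ct in condition 2 minus the Ct in condition 1, gene by gene. R is then a standard fold change between the two conditions, but the conditions named are the two cell states.
- *Reading B:* ΔCt is the Ct of the gene minus the Ct of GAPDH in one sample. Then ΔCt(GAPDH) = 0 and R = 2^-ΔCt(target), a level in one sample and not a change.

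**3. Illustration with assumed Ct values** (the article gives none):

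| | Target, Day 0 | Target, Day 56 | GAPDH, Day 0 | GAPDH, Day 56 |
|---|---|---|---|---|
| TRF volunteer | 28.0 | 27.5 | 18.0 | 18.5 |
| Placebo volunteer | 28.2 | 28.0 | 18.1 | 18.2 |

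*Reading A, with the trial's own Day 56 minus Day 0 put in:*
- TRF: 2^-((27.5 − 28.0) − (18.5 − 18.0)) = 2^-(−0.5 − 0.5) = 2^1 = 2.00
- Placebo: 2^-((28.0 − 28.2) − (18.2 − 18.1)) = 2^-(−0.2 − 0.1) = 2^0.3 = 1.23
- TRF relative to placebo: 2.00 / 1.23 = 2^0.7 = 1.62

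*Reading B, TRF volunteer:*
- Day 0: 2^-(28.0 − 18.0) = 2^-10 = 0.00098
- Day 56: 2^-(27.5 − 18.5) = 2^-9 = 0.00195
- Each figure is a level. The change, 0.00195 / 0.00098 = 2.0, appears only when a second step divides by Day 0, and the formula does not contain that step.

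**4. Can the algebra be kept?** Define ΔCt = Ct(target) − Ct(GAPDH) in each sample and ΔΔCt = ΔCt(Day 56) − ΔCt(Day 0). Rearranged,

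ΔΔCt = [Ct(target, Day 56) − Ct(target, Day 0)] − [Ct(GAPDH, Day 56) − Ct(GAPDH, Day 0)],

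which is the exponent of Reading A with the trial's contrast. In the illustration, ΔΔCt is 9.0 − 10.0 = −1.0 for TRF and 9.8 − 10.1 = −0.3 for placebo. The difference is −0.7, and 2^0.7 = 1.62 as before. The printed form therefore survives; only the contrast and the calibrator have to change.

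**The case against.** The strongest reply is that this is a local slip with the right answer beside it. The same subsection states the intended contrast, and the Statistical analysis section compares each parameter with baseline and/or placebo. The formula has a separate GAPDH term, which would be redundant under Reading B, so Reading A is the more natural one. With Day 56 minus Day 0 put in, it gives the intended fold change. All of this stands, and it limits the point to the contrast and the calibrator. It does not remove the point, because the reader must still replace what the defining sentence says.

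Two stronger readings are tempting and are not supported.

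- *That the formula returns a wrong answer.* A reader might note that a target 5 cycles above GAPDH on both days gives 2^-5 = 0.03 under Reading B, although the true fold change is 1.0. That sets a level against a fold change. The level is 0.03 on both days, and their ratio is 1.0, which is correct.
- *That the analysis is biased because ratios are skewed.* With no true change and assumed SDs of 0.5, 1.0 or 1.5 cycles, the mean ratio exp((SD × ln 2)²/2) is indeed 1.06, 1.27 or 1.72. But the article nowhere tests a ratio against 1, and it provides a rank test for skewed data. With equal spread and no effect, TRF and placebo share the same mean, so no difference between arms is created.

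It can also be said that the log2 scale and baseline adjustment are choices an analysis plan commonly makes, and that plan is not shown. That is fair: their absence is not an error. They are recommended below because they complete the replacement definition at no cost.

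**Conclusion.** The concern holds in a limited form. The defining sentence for gene expression names a contrast that does not occur in the trial and gives no calibrator for ΔCt. It contradicts the purpose stated in its own subsection and the blood source of the RNA. Under neither reading does the text as written yield the Day 0 to Day 56 change or the TRF-versus-placebo comparison.

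Severity is low. Gene expression is a secondary outcome and is not named in the four specific objectives. The primary outcomes and the sample size do not depend on it. The finding rests on the article's own statements; the Ct values above are assumed and only illustrate the algebra. That the sentence was carried over from another experiment is an inference, and the finding does not need it.

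**What to change.** Replace the closing sentence on the ratio with a definition in the trial's own terms:

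- ΔCt = Ct(target) − Ct(GAPDH) in each sample.
- ΔΔCt = ΔCt(Day 56) − ΔCt(Day 0) in each volunteer.
- Compare ΔΔCt, which is already on the log2 scale, between each TRF arm and placebo, adjusted for Day 0 ΔCt.
- Show 2^-ΔΔCt for display only.
- Treat within-arm change as descriptive. Table 1 of the article has every arm, placebo included, vaccinated on Day 28, so a Day 0 to Day 56 change within an arm combines vaccine and supplement.

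The change costs a few lines of text, to be settled before the expression data are analysed. The blood samples, PCR assays and number of volunteers stay as they are, and the Day 0 value used for adjustment is already collected.
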